#### Economic evaluation

Overall, costs associated with each participant will follow well established health economic principles [53], and cover direct medical costs of illness, plus the labor market effects of illness. Direct medical costs are to be calculated for prescription medications and hospital and health service contacts. Labor market productivity losses will be imputed using the human capital approach by multiplying reported days off work due to mental illness with an individual’s estimated salary using instrumentation devised by this team for a previous health economic evaluation [54]. Only using days off work due to illness to capture labor market costs captures an important aspect of the cost of illness; however, it is noted that the estimates obtained will be conservative and the true cost will be higher than what we obtain because of other effects of illness such as higher rates of non-participation in employment, or underemployment.

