### Aims and objectives

The aim of the PULSAR Primary Care study is to conduct a mixed methods evaluation of a training intervention for GPs in recovery-oriented practice. The purpose of the intervention is to optimize personal recovery in patients consulting project study GPs for mental health issues. The project employs an intervention mixed methods design [27], involving a stepped-wedge cluster randomized controlled trial (cRCT) of training in recovery-oriented practice, together with an embedded qualitative study of implementing recovery-oriented practice in primary care. Clusters are participating general practices and community health centers that employ GPs. The objective of the quantitative research is to examine whether adult patients of GPs and practices that have received training in recovery-oriented practice report greater personal recovery compared to other patients where practices have not received the intervention. The following research questions are addressed:From pre- to post-intervention, do patients of intervention cluster GPs report greater improvements on measures of personal recovery compared with control group patient participants?From pre- to post-intervention, do patients of intervention cluster GPs report greater improvements on measures of health and wellbeing status compared with control group patient participants?From pre- to post-intervention, do patients of intervention cluster GPs report greater improvements on measures of perceived need for care and satisfaction with services compared with control group participants?Are any changes in estimated service costs compatible with favorable health economic properties for the intervention?What are the contextual enablers and challenges to implementing recovery-oriented practice in primary care settings?

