### Intervention

The intervention consisted of training modules and optional ongoing participation in monthly webinars with participating GPs. Before development of the training materials, individual semi-structured interviews with GPs explored potential barriers to recovery-oriented training within primary care settings and this information was used to assist in design. The training intervention was designed in alignment with the modular training pathway of the General Practice Mental Health Standards Collaboration Mental Health Skills Training (MHST) requirements [38] and received accreditation for this as well as accreditation through the two relevant Australian GP Professional Colleges. Patients of GPs who have completed MHST can claim higher rebates for some mental health care activities Medicare.

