The two modules of the recovery-oriented training intervention delivered to participating GPs are: 1. Core Module (3.5 h) with learning objectives including increased skill in recognizing and assessing common mental illnesses within a recovery-oriented framework; a greater working knowledge of the Better Access initiative and mental health treatment planning with a focus on operationalizing recovery-oriented practice in general practice; enhanced understanding of the perspective of consumers and carers in the provision of mental healthcare; and increased knowledge of the local mental healthcare services and resources available to GPs; and 2. Clinical Enhancement Module (CEM; 4 h), which provides the opportunity to apply knowledge gained in the Core Module within the specific context of Schizophrenia. Learning objectives of the CEM include: development of skills in the detection and assessment of Schizophrenia; an ability to apply the principles of recovery-oriented practice to treatment planning and monitoring; the ability to develop recovery-focused mental health treatment plans; and an applied understanding of review processes and relapse prevention strategies for mental illness within a recovery-oriented practice framework. MHST criteria are met by participation in both modules, along with preparatory and reinforcing exercises. For GPs who already have MHST accreditation, the option is open to attend the CEM only, and one round of the training is delivered as something of a hybrid between the two but with full retention of the recovery-oriented practice content. In the latter two situations, GPs retain access to professional development points through their college but the MHST requirements do not need to be met.

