In addition to GPs, other clinic/practice staff such as practice nurses, non-participating GPs, and administration staff are also encouraged to attend training. Training is delivered by mental health clinicians, including experienced trainers from the study team, with co-delivery by consumer trainers. An experienced family/carer worker also participates, providing a minimum of one hour of content over the total of eight hours of training. The intervention draws heavily on the REFOCUS program [15] and the General Practitioner Mental Health Treatment Plan-Recovery (GPMHTP-R). The latter was developed in the Better Mental Health Treatment Plans Project, which was conducted by the Southern Synergy group with the support of a Commonwealth Government funding grant. The recovery-oriented training intervention includes training in the use of the GPMHTP-R, and also features locally developed materials. The intervention was developed following consultation and discussion with a group of local GPs (*n =* 7).

Each training participant is provided with resource material consisting of background reading and the Primary Care PULSAR Manual, which explains how to incorporate recovery-oriented practice into regular practice. The Project Team is responsible for developing, evaluating, and making these resources readily available. A schedule of training is provided to trainers, along with standardized training packs (including videos) to ensure the provision of standardized content. Trainers are asked to keep a record of training and to record any deviations from the schedule and use of materials.

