### PALS: PULSAR active learning sessions

GPs and other professionals who have received the PULSAR training are invited to participate in monthly one-hour online sessions called “PALS (PULSAR Active Learning Sessions)” with consultant specialist psychiatrists to review, reflect and share their experiences in the implementation of recovery-oriented practice. These sessions provide an interactive learning environment for supporting practice-based implementation of learning from the PULSAR resources and training package.

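### The stated cost scope has no line for delivering the training or PALS, so the planned costs cannot by themselves support a conclusion about the economic value of the intervention

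*Protocol article*

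**What the plan says.** The fourth research question under Aims and objectives reads: "Are any changes in estimated service costs compatible with favorable health economic properties for the intervention". The Economic evaluation section then says what each participant's costs are to include. They "cover direct medical costs of illness, plus the labor market effects of illness". The direct part is itemised: "Direct medical costs are to be calculated for prescription medications and hospital and health service contacts". The labor-market part is days off work multiplied by estimated salary. The section names one thing that it leaves out, namely lower employment and underemployment, and on that ground says that "the estimates obtained will be conservative and the true cost will be higher than what we obtain".

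The intervention itself uses resources that are described elsewhere in the article:

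- Two training modules, the first introduced as "Core Module (3.5 h) with learning objectives" and the second lasting 4 h. GPs who already hold Mental Health Skills Training (MHST) accreditation may take the second only.
- Clinician trainers, consumer co-trainers and a family/carer worker, the last "providing a minimum of one hour of content over the total of eight hours of training", together with manuals and training packs.
- PALS with consultant psychiatrists, offered as "monthly one-hour online sessions called" by that name. Attendance is optional.

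**The concern.** The economic question asks about the intervention, but the listed costs concern only illness and its treatment. Training and PALS consume the time of GPs, trainers, consumers, carers and psychiatrists, and they do so only where the intervention has been delivered. If the plan is followed as written, a finding that service costs fell or stayed level could be presented as a favorable economic result for the intervention, with its delivery cost implicitly set to zero. Such a result might not survive once delivery is counted, and a reader would have no way to tell, because the only under-count disclosed is on the illness side.

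**Working it through.** The article states no cost, unit price or cost-effectiveness figure, so there is nothing to reproduce. The check has two parts.

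**Is delivery cost inside the stated scope?** Four places were compared.

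1. The Economic evaluation section says what the costs cover and lists medications, hospital and health service contacts, and days off work. Delivery is not listed, and it is not named among the acknowledged omissions.
2. In the Measures section the economic items form part of the patient survey.
3. The Health Economics block of Table 2 holds only patient-level variables: medications, employment, income, days lost, admissions and consultations.
4. Table 3 places the health economic items under patient assessment. No row collects delivery resources for costing.

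The four agree, and delivery cost lies outside the stated scope.

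**How large might it be?** Only the hours come from the article.

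- Training per GP: 4 h (second module only), 3.5 + 4 = 7.5 h (both modules), or 8 h (the total given in the Intervention section, which differs slightly from the sum of the modules).
- PALS per GP: 0 h if none is attended, up to 9 h if every monthly session in one nine-month step is attended.
- GPs recruited: 30. Training time is therefore 30 × 4 = 120 h to 30 × 8 = 240 h in total, and PALS time 0 to 30 × 9 = 270 h.

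The price per GP hour and the number of patients over whom the cost is spread are assumptions: $100 to $250 per hour and 20 to 50 patients per GP.

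GP-time cost per patient = (training hours + PALS hours) × price per hour ÷ patients per GP

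- Low end: (4 + 0) × 100 ÷ 50 = $8.
- Both modules, no PALS: 7.5 × 100 ÷ 50 = $15.
- High end: (8 + 9) × 250 ÷ 20 = $212.50, about $210.

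The result scales directly with the assumptions. At $300 per hour and 10 patients per GP, the high end would be 17 × 300 ÷ 10 = $510. Spreading the cost over more patients of the same trained GP would lower every figure. Trainer, consumer, carer and psychiatrist time and materials would come on top.

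**The case against.** The strongest reply is that this is one paragraph in a condensed article. It describes costs per participant and appeals to established health economic principles. Training and PALS are programme-level costs that a fuller economic plan might treat separately. This has some force, and such a plan may exist. But the paragraph says what the costs cover and discusses one omission without mentioning delivery, so the scope is stated rather than merely left open.

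A second reply is that the research question concerns changes in service costs, and that no net benefit or cost-effectiveness ratio is promised. This stands in part. The service-cost comparison is valid without delivery costs. What fails is the further step, contained in the same question, to the economic properties of the intervention.

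Two stronger readings are tempting and are not supported.

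- **That the higher rebates are left out.** The Intervention section says: "Patients of GPs who have completed MHST can claim higher rebates for some mental health care activities Medicare". But health service contacts are costed, and neither a unit price nor a payer perspective is given, so omission is not shown. Some GPs already hold MHST accreditation, so their patients could claim the rebate in control periods too. GPs attending the second module only, or the hybrid round, need not meet the MHST requirements.
- **That the whole evaluation is tilted towards the intervention.** Leaving out lower employment and underemployment would understate savings if the intervention works, which pushes the other way by an unknown amount. Only the direction of this one omission is clear.

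Finally, the health economic questionnaire is listed under other measures in Table 1, so nothing here touches the primary analysis.

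**Conclusion.** The point holds in a limited form. The stated costs omit delivery of the training and PALS, so on their own they cannot show favorable economic properties of the intervention. Read as evidence of its value, the intervention-minus-control cost is too low by the full delivery cost. That cost is above zero and falls only in the trained condition. Its size cannot be derived from the documents. The figure of roughly $8 to $210 per patient for GP time alone rests on assumed prices and patient numbers, and its upper end assumes attendance at all nine PALS. With no illness-cost figure to set beside it, whether it would reverse a conclusion is unknown. The point deserves correction because the omission goes undisclosed and is easily repaired, but it is secondary to the trial's main question.

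**What to change.** Add a delivery-cost line to the economic evaluation, covering GP time, clinician trainers, consumer and carer co-delivery, materials, and PALS hours actually attended. Spread it over the patients exposed to trained GPs, and report the cost difference both with and without it. If this is not done, limit the economic conclusion to changes in service use and illness costs. In either case, state the payer perspective and the unit prices, including how rebates are treated.

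The cost is small. Trainers already keep a record of training, and actual training dates are recorded. PALS attendance must be confirmed separately, because the sessions are optional and the article does not say that attendance is logged. The net economic result will look somewhat less favorable than one without delivery costs.

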### Data collection and management

Table 3 outlines the data collected at each time point for participating GPs and patients. Patient participant data is being collected by the returned paper surveys or online surveys at three time points: baseline (months 4–6), Step 1 (months 16–18) and Step 2 (months 28–30), as displayed in Fig. 1. Both modes of survey completion are provided to offer flexible participation options. The estimated completion time for each round of surveys is approximately 45 min.

**Table 3 Tab3:** Schedule of enrolment, interventions, and assessments

	Time points			
Project events		T0	T1	T2
Intervention adaptation	X			
GP enrolment				
Eligibility screen	X			
Informed consent	X			
Randomization	X			
GP training intervention				
Year 1 clusters		X		
Year 2 clusters			X	
GP PALS				
Year 1 clusters		X	X	X
Year 2 clusters			X	X
Patient recruitment				
Eligibility screen by GP		X	X	X
Survey packs provided to eligible patients via GPs		X	X	X
Informed consent		X	X	X
Patient quantitative assessment				
Demographics		X	X	X
QPR		X	X	X
WEMWBS		X	X	X
INSPIRE		X	X	X
K10		X	X	X
Health economic items		X	X	X
GUPI		X	X	X
GP qualitative assessment				
Informed consent			X	X
Individual interview			X	
Individual interview/focus group				X
Patient qualitative assessment				
Informed consent			X	X
Individual interview			X	
Individual interview/focus group				X

The online survey option collects participant-entered data directly from Qualtrics online survey software. Qualtrics securely collects participant responses within a secure back-end spreadsheet that is only accessible by the researchers via password protected files.

If patient participants consent to allowing the researchers to access their routinely collected medical records, additional information will be extracted from these files with the assistance of the participating GP/s in each cluster site, including information about diagnosis and mental health status and medication details relating to mental health issues.

All study data is stored in re-identifiable format, from which identifiers have been removed and replaced by a code. Re-identification is necessary in order to link survey data with routinely collected data for patient participants who consent to the release of this information. Any personal information such as participant names remain confidential and all information is stored in password protected files and folders on password protected computers located at the core PULSAR administration site. These can only be accessed by the research staff. The study data will be stored for a minimum of 7 years, after this time it may be confidentially destroyed. It may be possible that future research such as a meta-analysis will use the participant data in non-identifiable format.

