**Methods:**

The intervention mixed methods design involves a stepped-wedge cluster randomized controlled trial testing the outcomes of training in recovery-oriented practice, together with an embedded qualitative study to identify the contextual enablers and challenges to implementing recovery-oriented practice. The project is conducted in Victoria, Australia between 2013 and 2017. Eighteen general practices and community health centers are randomly allocated to one of two steps (nine months apart) to start an intervention comprising GP training in the delivery of recovery-oriented practice. Data collection consists of cross-sectional surveys collected from patients of participating GPs at baseline, and again at the end of Steps 1 and 2. The primary outcome is improvement in personal recovery using responses to the Questionnaire about the Process of Recovery. Secondary outcomes are improvements in patient-rated measures of personal recovery and wellbeing, and of the recovery-oriented practice they have received, using the INSPIRE questionnaire, the Warwick-Edinburgh Mental Well-being Scale, and the Kessler Psychological Distress Scale. Participant data will be analyzed in the group that the cluster was assigned to at each study time point. Another per-protocol dataset will contain all data time-stamped according to the date of intervention received at each cluster site. Qualitative interviews with GPs and patients at three and nine months post-training will investigate experiences and challenges related to implementing recovery-oriented practice in primary care.

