## Methods

### Overall design

The intervention mixed methods design involves a stepped-wedge cluster randomized controlled trial testing the outcomes of training in recovery-oriented practice, together with an embedded qualitative study to identify the contextual enablers and challenges to implementing recovery-oriented practice within primary care settings. Eighteen general practices and community health centers were randomly allocated to one of two steps (9 months apart) to start an intervention comprising general practitioner training in the delivery of recovery-oriented practice. Data collection consists of cross-sectional surveys collected from patients of participating general practitioners at three time points: baseline, and again at the end of Steps 1 and 2 (see Fig. 1). A mixed methods design was chosen for a number of reasons, including that it would produce richer and more complete findings than that based on either the qualitative or quantitative approach alone. Combining these approaches can further explain and enhance the integrity of the project outcomes, so that a mixed methods design may assist with project credibility, particularly when multiple stakeholders are involved such as in the PULSAR project [28]. The use of qualitative and quantitative methods were integrated at different stages of the intervention trial [27]. Initially, qualitative methods were used in an exploratory manner to identify potential barriers to recovery-oriented training within primary care settings, and to inform the intervention design. Subsequently, quantitative methods are being used to then measure the effectiveness of the intervention. Following the intervention trial, qualitative methods will be used in an explanatory manner to gain a more nuanced understanding of GP experiences of implementing recovery-oriented practices and patient experiences of these practices [28]. Quantitative and qualitative data are collected from patient participants, but only qualitative data are collected from GP participants.

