#### Challenges with patient recruitment and retention

Initial patient recruitment by the cluster sites generated mixed results that varied from one cluster site completing baseline recruitment within one week to others not reaching their target after six months. Some clusters reported difficulties in identifying potentially eligible patients and a reluctance to mail to patients in case doing so jeopardized the practice/patient relationship. Other reasons for some cluster sites not distributing the survey to patients were: confusion about patient eligibility; believing the study was over or mistakenly thinking that the cluster had withdrawn from it; a lack of interest from patients in completing the surveys; and the required increase in administrative burden. Reasons given for being unable to identify eligible patients included resource pressures or having high numbers of patients that were either under the age of 18 or from culturally and linguistically diverse (CALD) backgrounds with low English proficiency.

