
## Statistical analyses

The recovery-oriented practice training intervention for primary care will be evaluated at the patient level by examining the surveys of adult patients who consult the participating GPs for mental health issues. The main evaluation plan is to examine the cross-sectional surveys returned by patients during three data collection periods: baseline, Step 1, and Step 2 (see Fig. 1).

The planned data collection schedule depends on the training intervention being delivered at each cluster in the scheduled month (see Fig. 1). As training delays in some clusters are expected, the following two main analysis approaches are planned to compare the post-intervention and control (pre-intervention) periods:Study planned dataset, which will use data collected from patients during the planned six-month periods centered on the midpoints of February 2015, August 2015 and November 2015 (see Fig. 1). Other data collected outside of these timespans are considered a protocol violation and are excluded from this dataset.Per-protocol all data dataset, which will use all available data time-stamped from date of intervention received at the cluster, as outlined in Table 3.

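### No rule requires a control survey to precede the cluster's training, and the printed Step 1 and Step 2 windows overlap by about three months, so some late-cluster surveys can carry the wrong exposure label

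*Protocol article*

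**What the plan says.** All places are in the protocol article.

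- **Data collection and management, Table 3** ("Schedule of enrolment, interventions, and assessments"). Under "GP training intervention", Year 1 clusters are marked at T0 and Year 2 clusters at T1. PALS is marked from T0 for Year 1 and from T1 for Year 2. The row "Survey packs provided to eligible patients via GPs" is marked at T0, T1 and T2. T0 is the Year 1 group's only control wave, and T1 is the Year 2 group's last one.
- **PALS: PULSAR active learning sessions.** "GPs and other professionals who have received the PULSAR training are invited to participate in monthly one-hour online sessions", so a PALS mark implies that training has taken place.
- **Explanation for choice of comparators.** A control site is one that has not yet had the intervention.
- **Overall design.** Surveys are taken at "baseline, and again at the end of Steps 1 and 2", with steps nine months apart.
- **Adaptations to design.** The nine months consist of three months of consolidation and six months in which patients are exposed.
- **Statistical analyses.** The planned dataset "will use data collected from patients during the planned six-month periods centered on the midpoints" of February, August and November 2015. A second, per-protocol dataset keeps all data and time-stamps it from the date the cluster received training.
- **Abstract, Methods.** "Participant data will be analyzed in the group that the cluster was assigned to at each study time point".
- **Main analysis plan, Table 2.** Intervention status turns to 1 only after a six-month lag. Time since intervention takes the value 0 for surveys within three months either side of training.

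**The concern.** In a design with two sequences and three waves, Step 1 is the only wave in which trained and untrained clusters are observed side by side, so it carries the randomized comparison. A late-cluster survey completed after training but counted as a Step 1 control pulls that comparison towards zero. An untrained survey counted as Step 2 intervention, or a trained survey counted in the early group's baseline, biases it in the same direction with less weight.

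Table 3 does not show that the control survey closes before training, and the rules for the planned dataset do not enforce it. The problem would also vary by site. Baseline recruitment ranged from "one cluster site completing baseline recruitment within one week to others not reaching their target after six months", so some sites spread their returns over the whole window while others finish at once.

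**Working it through.** **1. Windows as printed.** Taking mid-month ± 3 months:

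| Wave | Midpoint | Window |
|---|---|---|
| Baseline | Feb 2015 | about 15 Nov 2014 to 15 May 2015 |
| Step 1 | Aug 2015 | about 15 May to 15 Nov 2015 |
| Step 2 | Nov 2015 | about 15 Aug 2015 to 15 Feb 2016 |

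The midpoints are 6 and 3 months apart, against steps of 9 months in Overall design. Data collection and management gives months 4–6, 16–18 and 28–30, which are 12 months apart. Steps 1 and 2 overlap from about 15 August to 15 November.

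**2. What the overlap implies for late clusters.** These clusters should be untrained throughout Step 1 and trained throughout Step 2. Let training fall at date t and assume an even flow of surveys over each six-month window. Let p be the share of Step 1 surveys after t and q the share of Step 2 surveys before t.

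- t inside the overlap: p = (15 Nov − t)/6 and q = (t − 15 Aug)/6, in months, so p + q = 3/6 = 0.5.
- t before 15 August: p > 0.5 and q = 0.
- t after 15 November: p = 0 and q > 0.5.

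So p + q is at least 0.5 wherever t falls. Uneven flow changes the figure. It is zero only if no Step 1 survey comes after training and no Step 2 survey before it.

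**3. The nine-month structure instead.** With early training at month m, 3 + 6 months puts the Step 1 wave at m+3 to m+9 and late training at m+9. If the baseline wave closes at m, no control-wave survey follows training. The printed windows do not match this structure.

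**4. Table 2 coding.** On the same structure, the six-month lag switches status to 1 at m+6, the midpoint of the early group's Step 1 wave. With even flow, (6 − 3)/6 = 50% of those surveys would be coded as control, although Adaptations to design counts patients as exposed from month 3. Time category 0 mixes surveys from before and after training, so it cannot separate them.

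**5. Size.** Inputs from Sample size targets: SD 16, ICC 0.05, 20 clusters, 10 patients per wave (20 × 30 = 600, as stated), two-sided 0.05, power 0.80. The protocol gives no numeric target difference. A Hussey-Hughes cross-sectional model gives SE 2.47 and a detectable difference of 6.9 points, about 0.43 SD. The same model with 10 clusters gives 9.8 points, about 0.61 SD. Both agree with the medium to medium-large effect stated under Adaptations to sample size targets.

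Mislabelling only at Step 1 gives an expected estimate of (1 − pf) times the true effect:

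| pf | Effect retained | Power at 6.9 points |
|---|---|---|
| 0 | 100% | 80% |
| 0.10 | 90% | 71% |
| 0.25 | 75% | 56% |
| 0.50 | 50% | 29% |

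Mislabelling only at Step 2 with q = 0.5, or only at the early group's baseline with half its surveys carrying the full effect, retains 87% in either case. The values of p, q and f are assumptions; the protocol gives none of them.

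**The case against.** The strongest case is that no post-training control survey is shown to exist by plan. Table 3 gives no order within a column, so survey first, then training, then the start of PALS fits its marks. The scheduled training month is in Fig. 1, which is not shown here. Overall design places surveys at the end of steps and does not say whether they precede the next group's training. A survey returned after its window closes is excluded from the planned dataset, so slow recruitment alone does not mislabel anything. The per-protocol dataset re-stamps surveys by actual training date. If training fell at a window midpoint, an affected survey would be at most three months after it, inside both the consolidation period and the lag, where the plan expects little or no effect.

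Most of this stands. A reader might infer from Table 3 that trained patients are counted as controls by design, or that a quarter to a half of the effect is lost. The documents support neither: the order is not stated, and p = 0.5 is an assumption.

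Two parts do not answer the point. The three-month overlap comes from the printed midpoints and does not depend on how Table 3 is read. And the per-protocol dataset, if analysed with Table 2's status variable, still counts surveys from the first six months after training as control, which conflicts with the protocol's own definition of a control site.

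**Conclusion.** The point holds in a limited form. Table 3 does not separate the last control survey from training and PALS, and the planned dataset has no condition that would do so. With the windows as printed and surveys returned throughout them, some late-cluster surveys must carry the wrong label: trained as control, untrained as intervention, or both. Table 2's lag coding carries the problem into the per-protocol dataset.

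The size cannot be fixed from the documents. The Step 1 contrast keeps (1 − pf) of the effect. That is all of it if no Step 1 survey follows training or if nothing happens within the lag, and 75% or 50% of it at pf = 0.25 or 0.50, which would require training inside the window and an early effect. Fig. 1 may settle the order. If the printed midpoints are an error and training follows the close of each wave, p is near zero and what remains is the Table 2 coding and a clarification of Table 3.

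**What to change.** 1. Reconcile Table 3, Overall design, Adaptations to design, Statistical analyses (the three midpoints) and Data collection and management (the month ranges) on the order and dates of survey and training. Show in Table 3 which comes first within T0 and T1.
2. Count a survey as control only if it was completed before the cluster's training date. Use the scheduled date in the planned dataset, so that it stays as-assigned, and the recorded date in the per-protocol dataset.
3. Place surveys completed between training and the end of the stated consolidation or lag period in a transition category, left out of the control/intervention contrast. State one such period, since three and six months both appear, and align intervention status and time category 0 in Table 2 with it.

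The cost is small. Training dates are recorded (Intervention modifications and delays) and surveys are time-stamped (Table 2). The downside is the loss of some surveys returned close to training, mostly from slow sites; their number should be reported by cluster.
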